#### Protocol feasibility assessment

At the end of the experimental session, a survey will be administered to assess the complexity, length, and feasibility of the entire protocol. If the experience is considered too frustrating and tiresome, a simplification or reduction of the two tasks can be adopted after the first pilot recordings to increase both the comfort and interest of the young subjects.

#### Management

Participation to the study is voluntary and is always allowed to withdraw at any time without consequences. Each subject and their legal representatives will receive a privacy information sheet and a consent form. Subjects will be volunteers by self-selection and have sufficient cognitive status to provide informed consent, so vulnerable groups will not be considered in this research program. All subjects will have a one week washout period to consider participation in the study before informed consent is obtained. Once engaged in this longitudinal study, subjects will undergo the first physiatric visit. Confidentiality will be maintained throughout this study. All data collected by the researchers will be anonymous or anonymised prior to analysis. Demographic data on the participant will be included in the analysis of data, but this be presented in a way that provides no means to identify a natural living person.

There are no risks of harm to disclose, since all the measures are non-invasive.

The confidentiality and anonymity of the data will be guaranteed. At the end of the research period, the research data will be retained for further analysis and will not be sent to any third party.

All the staff involved in the research will be specialized personnel (e.g., physiatrists, neuropsychologists, physiotherapists, bioengineers), trained for the purposes of the research.

The ethical issues associated with the participation of (human) volunteers will be addressed through full compliance with the protection of personal data regulations, unobtrusive procedures, and maximum care for safety issues during field trials according to regulations in Italy and Europe.

#### Project timeline

Since this experimental protocol has already been approved from the Ethics Committee on April 2023 (n. 5627/AO/22), the study started in June 2023 and lasts two years. The laboratory setup will require two months (months 1–2). Data acquisition will be performed before treatment (T0) with the full-time brace (T0—months 3–7) and after 6 and 12 months (T1—months 9–13 and T2—months 15–19) full-time brace treatment and scoliosis-specific exercises (i.e., rehabilitation intervention—months 3–19). In parallel to subject recruitment (months 1–5) and data acquisition (months 3–7, 9–13, and 15–19), signal processing and interpretation (months 4–22) will be carried out to lead to the final stages of the project (months 20–24). The dissemination of results will not be limited to the final months of the project, but preliminary results after T0-data recording and processing (months 3–7) will be shared with academic and non-academic audiences through conference proceedings, seminars, and journal articles within the first year (months 9–13).

## Discussion

The innovative aspect of the proposed experimental protocol is the quantitative evaluation of girls with AIS before any treatment based on the combination of neurophysiological, postural and cognitive / behavior analyses, during the execution of exercises related to the body schema adapted for subjects with AIS. These will help us (i) investigate the neurophysiological processes underlying AIS and highlight neurophysiological biomarkers of disease progression; (ii) evaluate balance and target reaching performance and (iii) determine a routine battery of tests to monitor body representation alterations (i.e., body image and body schema) before treatment (i.e., partial or full-time brace and corrective postural exercises) and during/after treatment.

In our preliminary study [3], an increased theta activity and lateralized alpha activity were observed in central areas in AIS-adolescent girls during balance tasks. Increased theta power within central clusters may reflect a higher information processing load due to the increased postural demands caused by scoliosis, and alpha lateralization might be interpreted as a compensatory strategy to overcome sensorimotor dysfunction mirrored by altered body schema [3, 47, 48].

At T0, we expect significant differences in the EEG rhythms associated with postural control between adolescents with and without AIS, during upright stance and target reaching.

Our longitudinal protocol may highlight EEG alterations in AIS after 6 and 12 months of targeted therapy. We expect an improvement in the clinical condition of the subjects, produced by therapy, associated with neurophysiological changes: a decrease in theta rhythm due to decreased postural demands, and a reorganization of alpha rhythm over the sensorimotor areas.

Balance during upright stance is maintained through an accurate sensory input fusion integrated at different levels of the CNS and producing appropriate motor output. Postural control mechanisms in subjects with AIS need to be investigated further. Our previous study did not show balance alterations in adolescent girls with AIS, compared to healthy controls, when standing in upright position [3]. In the proposed experimental protocol, we plan to conduct a more in-depth analysis, evaluating balance conditions in subjects with AIS and CTRL, using data from IMU and force platforms. On the one hand, we expect similar balance performances in AIS and CTRL during the resting-state, complemented by unbalanced activation of the muscles on the right and left sides of the back, which may validate our hypothesis that adolescent girls with AIS adapt their brain activity to prevent scoliosis-causing large body movement. On the other hand, we foresee that the target reaching will highlight abnormalities in tuning the postural control in AIS compared to CTRL. Such abnormalities, combined with the mechanical effect of the scoliotic deformity, are expected to result in altered muscle activation symmetry, greater instability, and need for postural adjustments in AIS compared to CTRL groups. These findings will pave the way for the discovery of alterations in postural control mechanisms in adolescent girls with AIS.

Body schema refers to the sensorimotor body representation that entails tracking and updating the position and configuration of both body parts and other objects in space towards which reaching movements can be planned [27]. The functional representation of the action space immediately surrounding the body, also known as the peripersonal space, usually undergoes changes concurrent with body schema alterations. Through the target reaching we will assess if possible body schema alterations in adolescent girls with AIS can alter the planning of the movement within the peripersonal space. The forearm bisection task is a simple and common test widely used in clinical and research fields to investigate the body schema [27]. We will use this task to test whether adolescent girls with AIS have a different representation of the metric properties of their own body compared to CTRL. By replicating the same tasks at time T1 and T2, we will test how the body schema will change as a function of control postural exercises or the effectiveness of brace therapy. The first test of the body schema (T0) is expected to highlight a possible alteration in the perception of the shoulders-waist proportion and in the inclination of the trunk. We expect a decrease in alteration in their body representation due to the treatment. The two tasks are designed to reveal body schema alterations at T0 in the AIS group, which should improve significantly after the 6 month exercise and brace-treatment period (T1).

Cognitive and behavioral assessment will investigate two aspects of body image perception: how subjects perceive their body appearance and the emotional and cognitive aspects of body [26]. We expect to find significant differences between the AIS group compared to CTRL at T0, with AIS having a worse self-attitude towards body image (i.e. body image dissatisfaction). Worst score in the sub-domains of global severity index, body image concerns, avoidance and compulsive self-behaviors (BUT-A), and specific higher concerns for shoulders, chest, and hips than other body parts (BUT-B). Second, we expect to find body attentional bias in the AIS group towards disease-specific body parts (shoulders, back), meaning faster reaction time and higher accuracy in response to disease-relevant images, and particularly to own body-relevant images. At T1, we expect to find a significant improvement in self-attitude scores for body image compared to T0 and a reduction of the attentional bias towards disease-relevant body parts, which means no differences in reaction time and accuracy between relevant and irrelevant body parts.

A risk of the proposed experimental protocol is boredom and loss of interest and compliance due to its duration (circa 80 min) and complexity. If necessary, the protocol can be divided into three separate sessions on three different days. Block (i), blocks (iii-iv), and block (v) of the protocol are independent and investigate different research questions. Another possible risk is related to the longitudinal design. Adolescent girls with AIS may not be available to repeat neurophysiological, postural, and cognitive assessment after 6 and 12 months. To mitigate this risk, we will make our best efforts to retain subjects through periodic follow up; and we will increase the number of recruited individuals at T0 to take into account an approximately 20% dropout rate. Although not all individuals may complete all follow-up sessions, the protocol will still provide valuable data that will allow us to investigate the muscular and neurophysiological correlates of AIS compared to CTRL at enrollment (T0). The forearm bisection task, block (iv), and resting-state EEG recording can still provide us significant information regarding possible body schema alterations, neurophysiological patterns, and postural performances.

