### Procedure

All methods will be carried out in accordance with the guidelines of the 2008 Helsinki Declaration. Ethical approval has been obtained on April 2023. Written informed consent will be provided by both subjects and their legal guardians.

We estimate recruiting 40 subjects. Considering a 20% dropout (approximately 8 subjects), we expect to acquire data from 30 subjects (15 subjects with AIS and 15 CTRL). For the calculation, we used the average effect size observed in [3] (i.e., the minimum difference between CTRL and AIS subjects for the EEG laterality index in sensorimotor areas) considering error probability (*α*) of 5%, with a power (1 –*β* error probability) of 80%. Power statistical analyses will be repeated after having recorded data at T0 as an additional tool to review the required sample size. If necessary, the sample size will be enlarged.

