To reveal possible alterations in body image representation in adolescent girls with AIS, BUT sub-scores will be calculated (scoring instructions are reported in S1 Appendix). Response accuracy (i.e., percentage number of correct responses over the total number of trials) and reaction times (RTs), collected as outcome variables during the Computerized body self-recognition task, trials will be clustered according to the target stimulus and subsequently analysed. The correlations between the BUT questionnaire subscores and RTs and accuracy will be assessed using the Pearson’s correlation coefficient (r).

The results of AIS-adolescent girls and controls of the same age and sex will be compared by statistical analyses. Shapiro-Wilk normality test will be applied on all the data collected to check the normal distribution. A two-tailed paired sample t-test or a two-sided Wilcoxon rank sum test (*p* < 0.05) will identify differences between the two groups (AIS vs. CTRL) and between the three time points evaluation (T1, T0 and T2) after having run a global test (either repeated measure ANOVA, or Friedman test depending on data normality).

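### Similar resting balance is counted as support for brain adaptation, but the article's only group test looks for differences and, at 15 to 20 per group, cannot show similarity

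*Protocol article*

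**What the plan says.** In the Discussion of the Protocol article, the authors write that "we expect similar balance performances in AIS and CTRL during the resting-state, complemented by unbalanced activation of the muscles" on the two sides of the back, "which may validate our hypothesis that adolescent girls with AIS adapt their brain activity to prevent scoliosis-causing large body movement". Similar sway is thus one of two results named in that sentence as support for a mechanism.

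Under Foreseen data processing, resting balance is measured by COP range in the anterior-posterior and medial-lateral directions, sway path length and the 95% ellipse area. The resting block is recorded with eyes open and then closed. The group rule in the same section is "A two-tailed paired sample t-test or a two-sided Wilcoxon rank sum test" at p < 0.05, which "will identify differences between the two groups (AIS vs. CTRL) and between the three time points evaluation". The article gives no equivalence margin, equivalence test or confidence-interval rule.

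Under Procedure: "We estimate recruiting 40 subjects", and after dropout "we expect to acquire data from 30 subjects (15 subjects with AIS and 15 CTRL"). The effect size came from the EEG laterality index. A power review after T0 may enlarge the sample, but it is not tied to any balance measure.

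**The concern.** A test for differences can reject equality; it cannot establish it. If the authors apply the stated rule and find p > 0.05 for sway, the Discussion invites them to call balance similar and to count that towards brain adaptation. In a small study such a result is common even when a moderate deficit exists. The comparison at stake is the untreated one at T0, which the Project timeline plans to share within the first year. The article would then have an uninformative null on record as part of the evidence for a mechanism.

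**Working it through.** **The plan's own figure.** The 15 per group cannot be rebuilt because the effect size is not given as a number. Working backwards, 15 per group at two-sided 5% and 80% power corresponds to a standardised difference of 1.06 (independent-samples t-test). The sample therefore suits differences of about one SD. On attrition, 40 × 0.8 = 32 against the stated 30, which is close enough not to matter here.

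**Inputs.** From the article: 15 per group after dropout; about 20 per group if all 40 are measured at T0; two-sided 5%. Assumed, because the article gives no SD, effect or margin for balance: true deficits of 0.5 and 0.8 SD, and margins of 0.5, 0.8 and 1.0 SD. AIS and CTRL are treated as independent groups.

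**Chance of missing a true deficit, per COP measure.** Power is P(|T| > t(0.975; 2n − 2)), where T is noncentral t with noncentrality d√(n/2). For n = 15 and d = 0.5 the noncentrality is 0.5 × √7.5 = 1.37 and power is 0.262, so the miss rate is 1 − 0.262 = 0.738.

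| True deficit | Missed, 15 per group | Missed, 20 per group |
|---|---|---|
| 0.5 SD | 74% | 66% |
| 0.8 SD | 44% | 31% |

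**Precision.** The CI half-width in SD units is t × √(2/n).
- n = 15, 95%: 2.048 × 0.365 = 0.75. 90%: 1.701 × 0.365 = 0.62.
- n = 20, 95%: 2.024 × 0.316 = 0.64. 90%: 1.686 × 0.316 = 0.53.

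**Could equivalence be shown?** Two one-sided 5% tests, true difference zero, 200,000 simulations:

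| Assumed margin | 15 per group | 20 per group |
|---|---|---|
| 0.5 SD | 0.6% | 3% |
| 0.8 SD | 38% | 60% |
| 1.0 SD | 70% | 86% |

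At a 0.5 SD margin the typical 90% half-width (0.62 or 0.53) already exceeds the margin, so the interval can fit only when the sample SD comes out low. By the normal approximation, 80% power at that margin needs 2 × (1.645 + 1.282)² / 0.5² ≈ 69 per group.

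**The case against.** The strongest reply is that this is hedged Discussion text about a secondary matter, and that margins and interval reporting are details an article may leave to an analysis plan not shown here. That lowers the severity. It does not remove the point, because the article itself states both the inference and the test, and the two do not fit.

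Some stronger readings are tempting, but the documents do not support them:

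- *A smaller or noisier study would validate the hypothesis more easily.* The sentence also requires muscle imbalance, a positive finding that gets harder to show as n falls. Assume a 0.5-SD sway deficit, a 0.8-SD muscle effect and independence. The chance of non-significant sway together with significant imbalance then rises with n: 18% at 5 per group, 32% at 10, 41% at 15 and 46% at 20.
- *Non-significance is likely whatever the true deficit.* This holds per measure for moderate deficits only. There are eight resting COP results (four measures, eyes open and closed). With pairwise correlations assumed at 0.5 to 0.9 and 15 per group, all eight are non-significant in about 32% to 58% of studies at 0.5 SD, but in only about 7% to 27% at 0.8 SD.
- *The Discussion concedes that deformity alone alters muscle symmetry, with no brain adaptation.* It does not. It names the mechanical effect jointly with abnormal postural control, and in the context of target reaching.
- *The hypothesis rests on no brain measure at all.* The sentence names none, but slightly earlier the Discussion expects EEG differences at T0 during upright stance, and the resting block records EEG together with COP.

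It is also fair that 15 per group is the figure after dropout and that up to about 20 per group may be measured at T0. The results for 20 are given above and lead to the same conclusion.

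**Conclusion.** The point holds as a minor one. The article counts similar resting balance, together with muscle imbalance, towards brain adaptation, while its only group rule is a difference test at 5%. With 15 to 20 per group, a non-significant COP comparison leaves differences of roughly 0.64 to 0.75 SD either side of the estimate unexcluded. It misses an assumed 0.5-SD deficit in 66% to 74% of studies per measure. Similarity within 0.5 SD is practically out of reach; only margins of about 0.8 to 1.0 SD offer a realistic chance. These sizes rest on assumed effects and margins. That the authors would equate p > 0.05 with similarity is inferred from the absence of any other stated rule.

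**What to change.** - Under Foreseen data processing, state that resting COP differences (AIS minus CTRL) will be reported with 95% CIs.
- State that balance will be called similar only if the 90% CI lies within a margin fixed before the T0 analysis. Otherwise report that no difference was detected and that differences up to the CI limit are not excluded.
- In the Discussion, reword the sentence so that a non-significant sway comparison does not count as support for brain adaptation. Rest that hypothesis on the EEG differences in upright stance that the article already expects. Report any EEG-sway association as exploratory, with its CI.

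This needs only wording and interval reporting on data already to be collected. The price is that the similarity claim will probably have to be given up at this sample size. A formal group-by-EEG interaction model is not needed and would itself be underpowered here.

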## Conclusion

Investigating a defective postural-CNS control and body representation alterations in AIS is a key step toward the identification of the pathogenic mechanism underlying scoliosis. The proposed protocol has utility for future studies in which datasets of different nature should be collected and interpreted in adolescent girls with AIS. This experimental protocol that aims to integrate cerebral, muscular, postural, cognitive, and behavioral data may (i) enrich current routine exams performed in clinical practice, (ii) offer novel therapeutic targets according to identified pathophysiological patterns, and (iii) contribute to advance scientific knowledge in neuroscience, musculoskeletal disorders, and rehabilitation.
